# A cluster randomized trial for the implementation of an antibiotic checklist based on validated quality indicators: the AB-checklist

**DOI:** 10.1186/s12879-015-0867-2

**Published:** 2015-03-19

**Keywords:** Checklist, Antibiotics, Implementation, Quality indicators, Stepped-wedge design

## Abstract

**Background:**

Recently we developed and validated generic quality indicators that define ‘appropriate antibiotic use’ in hospitalized adults treated for a (suspected) bacterial infection. Previous studies have shown that with appropriate antibiotic use a reduction of 13% of length of hospital stay can be achieved. Our main objective in this project is to provide hospitals with an antibiotic checklist based on these quality indicators, and to evaluate the introduction of this checklist in terms of (cost-) effectiveness.

**Methods/Design:**

The checklist applies to hospitalized adults with a suspected bacterial infection for whom antibiotic therapy is initiated, at first via the intravenous route. A stepped wedge study design will be used, comparing outcomes before and after introduction of the checklist in nine hospitals in the Netherlands. At least 810 patients will be included in both the control and the intervention group. The primary endpoint is length of hospital stay. Secondary endpoints are appropriate antibiotic use measured by the quality indicators, admission to and duration of intensive care unit stay, readmission within 30 days, mortality, total antibiotic use, and costs associated with implementation and hospital stay. Differences in numerical endpoints between the two periods will be evaluated with mixed linear models; for dichotomous outcomes generalized estimating equation models will be used. A process evaluation will be performed to evaluate the professionals’ compliance with use of the checklist. The key question for the economic evaluation is whether the benefits of the checklist, which include reduced antibiotic use, reduced length of stay and associated costs, justify the costs associated with implementation activities as well as daily use of the checklist.

**Discussion:**

If (cost-) effective, the AB-checklist will provide physicians with a tool to support appropriate antibiotic use in adult hospitalized patients who start with intravenous antibiotics.

**Trial registration:**

Dutch trial registry: NTR4872

## Background

### The need to improve antibiotic use

The increasing antimicrobial resistance rate is one of the most important health care problems at this moment. The total consumption of antibiotics is the main driving force [1,2]. The World Health Organization signalled the emergence of antimicrobial resistance (AMR), along with the steady decline in the discovery of new antimicrobials, as a major health threat for the coming decade. To help control AMR, a better use of the current agents is necessary [3]. Recent studies have shown considerable room for improvement in the two most common bacterial infections: respiratory and urinary tract infections [4,5]. An important question is how to achieve such an improvement.

Previous studies have shown that appropriate antibiotic use is not only of great importance to curb antimicrobial resistance, but also has a short-term consequence. The evaluation of antibiotic treatment for urinary tract infections in hospitals showed an inverse relationship between the proportion of appropriate antibiotic use in a patient and length of stay (LOS). Prescribing therapy in accordance with local hospital guidelines was associated with a shorter LOS (7.3 days vs. 8.7 days; P = 0.024) [6]. Recently a similar inverse relationship has been shown between appropriate antibiotic use in treatment of all bacterial infections in the hospital and LOS, with a reduction of 13% in LOS with appropriate use. [*Abstract poster:* Quality Indicators for Monitoring Appropriate Antibiotic Use in Hospitals: an Important Tool for Antibiotic Stewardship. K-325. *54th Interscience Conference on Antimicrobial Agents and Chemotherapy, September 5 -9, 2014, Washington DC*].

### Quality indicators

Guidelines defining appropriate antimicrobial treatment are available. To measure whether guideline recommendations are implemented in daily practice, an instrument is needed that validly measures the quality of antibiotic use in daily clinical practice. Guideline-based quality indicators (QIs) are such tools. Recently, generic QIs for the antimicrobial treatment of bacterial infections in hospitals have been developed and validated [7]. The challenge is the embedding of appropriate antibiotic use, as defined by these QIs, in daily practice.

### Checklist

A checklist can be a tool for implementation; since it has been shown in other high-risk disciplines that adherence to checklists increases safety [8]. This also holds true for the field of medicine. For example, in surgery, implementation of a comprehensive multidisciplinary SURgical PAtient Safety System (SURPASS) is associated with an absolute risk reduction in surgical complications of 10.6% [9]. Similarly, the introduction of a checklist to improve patient care among gynaecologic oncology patients has resulted in a decreased length of stay of one day (4.5 days in the pre- and 3.5 days in the post-implementation period (P = 0.007)) [10]. In the field of infectious diseases, Pronovost et al. showed that introduction of a five-points checklist to reduce infections when inserting a central venous catheter, resulted in a decrease of the median rate of infections from 2.7 per 1,000 patients to zero after three months [11].

We hypothesize that an antibiotic checklist, to be used at the start of antibiotic treatment and after 48-72 hours of treatment, will improve clinical patient care, reduce costs and will ultimately contribute to the containment of antimicrobial resistance.

### Objectives

This study is set to implement an antibiotic checklist based on the validated generic quality indicators measuring the appropriateness of intravenously initiated antibiotic use in hospitalized adults treated for a suspected bacterial infection, and to analyse the effect of the introduction of the checklist on patient care in terms of shorter duration of intensive care unit (ICU)- and hospital stay, adequate treatment, decreased mortality rates, decreased total antibiotic use and lower costs.

## Methods and design

### Phase 1: The AB-checklist and barriers for use

The ‘Development of reliable generic quality indicators for the optimization of antibiotic use in the hospital’ (RIANT)-study used a RAND modified Delphi method to develop a set of generic QIs for appropriate antibiotic use in the treatment of all bacterial infections in hospitalized adult patients [7]. The clinimetric properties of these QIs have been tested in 1,890 hospitalized patients, in 22 Dutch hospitals. This analysis resulted in eight useful QIs, of which seven were process indicators that focus on the actual care provided. The antibiotic checklist includes these seven QIs.

The antibiotic checklist is intended as a reminding tool for the physician who starts intravenous (IV) antibiotic treatment. It is actually divided into two bundles (Figure 1). The first bundle has to be completed at the moment of prescribing IV antibiotics, and comprises five items. The second bundle is used during the course of treatment, at the latest after 72 hours of treatment. This part consists of two items.

**Figure 1 Fig1:**
[figure not shown]
**The antibiotic checklist.**

As a preparation, we identified barriers of implementing this checklist, using a questionnaire based on an instrument of the Netherlands Organization for Applied Scientific Research (TNO), which is designed to survey determinants that influence the uptake of an innovation in health care organizations [12,13]. The questionnaire was sent to specialists and residents who work at the participating hospitals. Based on the identified barriers, the checklist design and its implementation format were adapted.

### Phase 2: cluster randomized clinical trial to evaluate the AB-checklist

#### Study design and setting

The (cost-) effectiveness of introducing the antibiotic checklist will be studied in a controlled, multicentre, prospective study using a stepped wedge design, comparing outcomes before and after implementation of the checklist while accounting for potential confounders [14].

The checklist will be introduced in nine hospitals over four time periods, during a total study period of eleven months (Figure 2). The aim is to include at least 810 patients in the period before- (the baseline group), and at least 810 patients with a completed checklist in the period after checklist introduction (intervention group). During the transition period implementation activities will be started and no patients will be included. This period runs from one month before introduction of the checklist to one week after introduction. Since compliance to the checklist will not be 100%, we will also collect data concerning the LOS from the patients in whom the checklist should have been but was not completed during the period after checklist introduction (the spill over group).

**Figure 2 Fig2:**
[figure not shown]
**The stepped wedge design for checklist implementation.**

To promote selection of a patient population representative for every day clinical practice in the Netherlands, two university hospitals and seven teaching hospitals will participate, and in each hospital at least one surgical and one non-surgical ward will be included. The ICU and the paediatric ward will be excluded, as the quality indicators do not apply to these populations. Patients with a suspected bacterial infection presenting on the emergency department (ED) will be included if they are going to be hospitalized on one of the participating wards.

#### Intervention

The study coordinator will design a project plan together with the local project leader. This plan will focus on physicians, nurses and medical students who are involved in patient care. The plan will include standard items (see Table 1), but additional items can be added, if locally required, to cover practical issues as for example: How do we arrange that for each patient starting with antibiotics intravenously a checklist is filled in? How do we arrange that the checklist does not get lost?

**Table 1 Tab1:** **Description of activities to stimulate use of the antibiotic checklist**

**Activity**	**Details**	**For whom**	**When or how**
**Education, including feedback**	About the need of appropriate antibiotic use and the room for improvement in current antibiotic use based on the baseline measurement; About the guidelines, adaption to renal function and IV-oral switch.	Physicians, medical students	Kick-off meeting; Website, e-learning
**Reminders**	Laminated pocket versions; posters	Physicians	During the whole intervention period
**Involvement of the whole health care team**	Involvement of a supervisor of each participating department in the implementation process	Physicians	Prior to implementation and during implementation
	Informing nurses about the study project	Nurses	e-mail, website, e-learning
	Informing medical students about the study project	Medical students	Letter, website, e-learning

### Patient enrolment

#### Eligible patients

The physician will use the checklist in all hospitalized adults (≥18 years old), or adults at the ED who will be admitted at a participating ward, with a suspected community-acquired and/or hospital-acquired bacterial infection, and will be treated with intravenous antibiotics. The treating physician identifies these patients upon prescription of antibiotic therapy. The patients included in the study are all patients that meet the above mentioned inclusion criteria, whether they have a completed checklist or not (see Figure 3 for the flowchart). They will be included in each hospital using an overview of the patients who started with intravenous antibiotics. This overview will be generated by the local departments of hospital pharmacy from the computerized physician order entry systems. Patients are excluded from the study in case of anticipated hospital stay of less than 24 hours, antibiotics used as prophylaxis or intended for less than 24 hours, hospitalization at the ICU at the start of the treatment, transfer from another hospital, or antibiotic treatment in the ambulance before presentation at the ED.

**Figure 3 Fig3:**
[figure not shown]
**Flowchart of the included patient in our study.**

### Primary and secondary endpoints

The primary endpoint is length of hospital stay in days. LOS in community-acquired infections will be defined as the number of days between admission and discharge. In hospital-acquired infections LOS will be defined as the number of days between start of antibiotic treatment and discharge. Secondary endpoints are appropriate antibiotic treatment according to the generic QIs (yes/no per QI and sum score of all QIs) [6], admission to and duration of ICU stay in days, readmission within 30 days, mortality in the hospital and in the first 30 days after discharge, total antibiotic use, costs of hospital stay and costs associated with implementation.

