### Assessments

For patient outcome we will collect data concerning the LOS, admission to and duration of ICU stay, readmission within 30 days and mortality in hospital or within 30 days after discharge for the baseline group and the intervention group. Furthermore we will collect data for possible confounders of patient’s outcome, namely age, sex, community-or hospital acquired infection, Charlson comorbidity index [15,16], use of antibiotics during the previous 30 days, and clinical condition as assessed by the Modified Early Warning System [17]. To calculate QI performance we will collect data concerning the number of taken blood cultures including its results, the number of taken cultures of suspected sides of infection including its results, antibiotic use including dose, interval and duration of treatment in days, the (suspected) type of infection and relevant laboratory parameters. For the spill over group, we will only collect data concerning the LOS and the possible confounders.

Antibiotics included in the study belong to group J01 (antimicrobials for systemic use) of the Anatomic Therapeutic Chemical (ATC) classification system. When multiple antibiotics are prescribed to one patient, all antibiotics will be registered. Antiviral therapy, medication for tuberculosis, antibiotics used for non-systemic selective intestinal decontamination and antibiotics used as pro-kinetics will be excluded.

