### Analysis

#### Effect evaluation

We will use mixed linear models to analyse the overall effect of the introduction of the checklist on length of stay. Therefore we will evaluate differences between baseline (before introduction of the checklist) and intervention plus spill over (after introduction of the checklist) (intention to treat analysis). We will also determine the theoretical effect of the checklist on LOS by evaluating differences between baseline and intervention data without the spill over data (per protocol analysis). Differences between the baseline data and the intervention data for secondary outcomes will also be evaluated with mixed linear models. For dichotomous outcomes (mortality), the comparison will be evaluated with a similar approach, using generalized estimating equation models. These mixed models account for within-cluster dependencies, and allow adjustment for possible confounders. To assess whether differences between these groups may be explained by confounding patient characteristics, we will first test with multivariate multilevel (linear mixed) analyses if these variables have a significant effect (p < 0.05) on the outcomes. Hereafter, we will compute the estimate of the total causal effect of checklist implementation on the outcomes before and after adjusting for a significant variable. If the estimate varies 10% or more, possible confounding is present and in that case we will adjust for this variable.

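### Length of stay ends at discharge with no vital status for the spill-over group, so in-hospital deaths cannot be handled evenly; the mortality window also moves with discharge, to small effect

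*Protocol article*

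**What the plan says.** All places are in the protocol article.

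- **Primary endpoint** (Primary and secondary endpoints): "The primary endpoint is length of hospital stay in days". Two definitions follow. The first is "LOS in community-acquired infections will be defined as the number of days between admission and discharge"; the second is "In hospital-acquired infections LOS will be defined as the number of days between start of antibiotic treatment and discharge". Both stop at discharge, and neither mentions death.
- **LOS analysis** (Effect evaluation): mixed linear models, comparing baseline with "intervention plus spill over (after introduction of the checklist) (intention to treat analysis"). No censoring or competing event is named.
- **Mortality** (Primary and secondary endpoints): a secondary endpoint, given as "mortality in the hospital and in the first 30 days after discharge". Assessments restricts its collection: "mortality in hospital or within 30 days after discharge for the baseline group and the intervention group".
- **Spill-over group** (Assessments): "For the spill over group, we will only collect data concerning the LOS and the possible confounders". The confounders listed there are age, sex, origin of infection, comorbidity index, recent antibiotic use and early warning score. Vital status is not among them.
- **Expected direction** (Objectives): the aims include "shorter duration of intensive care unit (ICU)- and hospital stay, adequate treatment, decreased mortality rates", so both LOS and mortality are expected to fall.

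**The concern.** LOS and death are competing ways for a hospital stay to end, and no simple handling of death is neutral. If the day of death closes the stay, an early death is scored as a short stay. An averted death then adds a longer stay to the post-introduction group and hides part of an LOS benefit, while an extra death has the opposite effect and resembles a benefit. If deaths are left out, the comparison is restricted to survivors, a group that the intervention may itself change.

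This would normally be left to the analysis plan. Here the data collection limits what that plan could do. Patients without a completed checklist count in the intention-to-treat LOS comparison, but whether they left hospital alive is not among the items collected for them.

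The mortality endpoint has a related weakness. Its window closes 30 days after discharge, an event that the checklist is meant to bring forward, so a group with shorter stays is watched for less time.

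At stake is the reading of the primary result, and also the cost-effectiveness ratio in Economic evaluation, which is expressed per day of LOS reduced.

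**Working it through.** **Inputs from the article.** Target reduction 13% (Sample size). LOS 8.7 and 7.3 days, from the two groups of the urinary tract infection study in the Background; these serve only as a scale, since no LOS is given for this trial's mixed population. Planned size 9 × 180 = 1620 = 2 × 810, which agrees with the article. The stated power of about 80% cannot be checked, because no standard deviation for LOS is given; nothing below depends on it.

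**Assumed inputs.** In-hospital death rates, day of death and stay lengths by outcome are not in the article. They are varied below.

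**1. Target in days.** 0.13 × 8.7 = 1.13 days.

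**2. Shift in mean LOS if death ends the stay.** For a mortality change Δ, shift = Δ × (stay if the patient survives − stay if the patient dies). With Δ = 2 percentage points:

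- Survivor stay 8.7 days, death on day 5: 0.02 × 3.7 = 0.07 days, or 7% of 1.13.
- Survivor stay 8.7 days, death on day 3: 0.02 × 5.7 = 0.11 days, or 10%.
- Averted deaths were 6-day stays and become 15-day stays: 0.02 × 9 = 0.18 days, or 16%.
- Averted deaths were 6-day stays and become 20-day stays: 0.02 × 14 = 0.28 days, or 25%.

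A fall in mortality masks LOS benefit by these amounts. A rise of the same size mimics benefit, provided the added deaths would otherwise have had the stay assumed in that line.

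**3. Could deaths create the whole effect?** Assume 5% baseline in-hospital death and survivor stay 8.7 days. The increase needed is 0.13 × baseline mean ÷ (8.7 − day of death):

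- Death on day 1: baseline mean 8.315, and 0.13 × 8.315 ÷ 7.7 = 14 points.
- Death on day 3: baseline mean 8.415, and 0.13 × 8.415 ÷ 5.7 = 19 points.
- Death on day 5: baseline mean 8.515, and 0.13 × 8.515 ÷ 3.7 = 30 points.

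**4. Who can be classified as dead or alive at discharge?** Baseline: yes. Completed checklist: yes. Spill-over: no, on the items listed. Excluding deaths, treating death as a competing event and ranking deaths worst all require each death to be recognised, so none can be applied to the whole intention-to-treat comparison. Only letting death close the stay needs no vital status. That is the choice with the distortion in step 2, and its extent could not be examined in the spill-over group.

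**5. Mortality window.** For a patient discharged alive, follow-up is LOS + 30 days.

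- At LOS 8.7: 38.7 days before; 0.87 × 8.7 + 30 = 37.6 days after; a loss of 1.13 days (2.9%).
- At LOS 7.3: 37.3 to 36.4 days (2.5%).

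With a constant hazard and no true effect, apparent mortality becomes 1 − (1 − p)^(37.57/38.7). Assumed p of 5, 10 and 15% becomes 4.86, 9.72 and 14.60%, a spurious drop of 0.14, 0.28 and 0.40 percentage points. With 810 per group and clustering ignored, the chance of a significant result in that direction is about 3 to 4%, against 2.5% with no difference (two-sided 5% level assumed).

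**The case against.** The strongest reply is that a death rule for LOS is a detail that a condensed article leaves to the full protocol or analysis plan, so its absence is no finding. That stands for the rule alone. It does not dispose of the point, because the items collected for the spill-over group and the discharge-anchored mortality window are both stated in the article, and the first limits which rules a later plan could apply.

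A reader might infer that the plan counts deaths as short stays. The article does not say so; it is one reading of a definition that stops at discharge, and exclusion is another.

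The sizes in days rest on inputs that the article does not supply, and the 8.7-day figure comes from a narrower population. This is correct. The upper part of the range (16 to 25%) needs averted deaths to become stays of 15 to 20 days; average stays give 7 to 10%. Neither can be preferred from the text.

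The mortality window effect is numerically minor. This also stands. A hazard that falls with time since infection would make it smaller still, and the in-hospital part can be read separately.

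There are partial safeguards: patients in the ICU at start of treatment are excluded, severity and comorbidity are recorded, and mortality is an endpoint in its own right. They help interpretation, but the mortality comparison leaves out the same spill-over patients, so it cannot show whether deaths shifted LOS in the full intention-to-treat comparison.

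**Conclusion.** The point holds in a limited form. As written, the intention-to-treat LOS comparison includes patients whose deaths are not recorded, so no rule that treats deaths separately can be applied evenly across it. The remaining option lets a mortality change move LOS in the misleading direction. Under the assumed death rates and stays, a 2-point change is worth about 0.07 to 0.28 days, roughly 7 to 25% of a 1.13-day target. That is enough to blur the primary result but not to produce it: 14 to 30 extra points of in-hospital death would be needed for the full 13%, so the stronger inference that deaths could manufacture the effect is not supported.

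The mortality window is a definition flaw of low weight: about 1 day in 38, or roughly 0.1 to 0.4 percentage points at an assumed 5 to 15% mortality under a constant hazard. A reader should not infer from it that the mortality comparison is seriously biased.

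**What to change.** 1. Record vital status at discharge for the spill-over group.
2. Keep the mixed linear model as the primary LOS analysis, but state how an in-hospital death enters LOS, identically for all three groups.
3. Add one sensitivity analysis on the intention-to-treat set: time to live discharge with death as a competing event or, more simply, in-hospital deaths given the worst LOS rank.
4. Count mortality within a fixed 30 days from start of antibiotics, and keep the discharge-anchored figure as descriptive. Antibiotics start before discharge, so the planned follow-up to 30 days after discharge already covers this window.

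**Cost.** One extra data field for the spill-over group, which is a change to data collection and not only to wording; one extra analysis to report; and confirmation that dates of death are recorded, since Assessments lists mortality but not its date. Sample size, primary model and patient care are unchanged.
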